**S1 Protocol. Study Protocol.**

**Improving the Quality of Asthma Control Using the Internet**

**Research Proposal**

## Specific aims or objectives

In the US, asthma affects approximately 15 million people, including 5 million children 1. The direct plus indirect costs of asthma, including lost productive time in the US are estimated to be greater than 12 billion dollars annually 2,3. Of this, at least 2.5 billion dollars of lost productivity is estimated to be due to the suboptimal care that patients with asthma receive 4. Despite widespread dissemination of evidence-based guidelines, more than half of adults with asthma have uncontrolled asthma 5,6. For example, Schatz and colleagues noted, among a random sample of adult patients with asthma who had health insurance, 51.7% had uncontrolled asthma 5. This lack of control is seen despite a large increase in the percentage of adults with asthma who use a controller medication 7,8. In addition to poor asthma control, several recommendations from the National Asthma Education and Prevention Program (NAEPP) guidelines, published since 1991, have not been consistently followed. The 2003 National Asthma Survey, for example, observed that only 55% of adults with asthma were taught to recognize early symptoms of asthma, only 47% were instructed to change their environment to improve asthma control and only 33% had ever received an asthma action plan 9,10. Though patient non-adherence to controller medicines likely contributes to poor asthma control, lack of asthma control likely reflects a widely observed tendency of physicians to make no changes in the face of patients who have not met a treatment goal for a chronic illness, known as “clinical inertia” 11-15. One intervention strategy that has proven effective in improving care is prompting patients to ask their providers specific questions that lead to changes in their care 16-20. This strategy is effective because patients who ask for tests and treatments tend to get them 21,22. This strategy has been widely successful in studies aimed at improving preventive care (e.g., pap testing), though its effects on improving chronic illness care, including asthma, have not been studied 16,23. Without an intervention, however, patients do not know the questions to ask that will lead to improved chronic illness care 24. To test the efficacy of this approach for improving asthma care, we have developed an interactive website to be used by patients with asthma at least once each month, during exacerbations and before asthma care provider visits 25. The program asks patients questions about their asthma symptoms, disability from asthma, the names and doses of asthma medicines and about the care they’ve received for asthma. Based on responses to these questions and decision rules from the 2007 NAEPP Guidelines 26, patients are given personalized feedback. The feedback includes questions that the patient should consider asking during their next doctor visit, along with a lay explanation of why they should ask each question and links to reputable websites (e.g., www.nhlbi.nih.gov) to learn more about each suggested question. Sample questions that patients are encouraged to ask include: “Would I benefit from using an inhaled corticosteroid to control my asthma?”, "What medicine change would help to control my asthma?” and “Should I have a prescription for steroid pills to have at home if my asthma worsens?”. The interactive website is designed to activate patients to ask questions that may improve the quality of care they receive for asthma. Previous studies have shown that the interactive website leads to important changes in what happens during doctor visits, that both physicians and patients find the interactive website useful and empowering to patients and that the feedback does not harm the doctor-patient relationship 25,27,28. In order to build upon those positive findings, we propose an efficacy study to test the effect of this approach for improving asthma care and control. We will enroll 408 adult patients from a large health plan in Pennsylvania and randomize them to use the asthma module (IC) or the adult preventive services module (CC) of the interactive website for a period of 12 months. Primary Hypothesis: is to determine the efficacy of having patients use the asthma module of the interactive website to improve asthma control, based on the Asthma Control Test (ACT). After 12 months, we hypothesize that 70% of patients in the IC condition will have their asthma controlled (ACT ≥ 20) versus only 55% of patients in the CC condition. Secondary Hypothesis: is that at the end of 12 months, we hypothesize that IC subjects, compared to CC subjects, will have greater improvements in: a) asthma-related emergency department visits, b) asthma related quality of life, c) pulmonary function, d) controller/reliever medication ratio, e) satisfaction with asthma treatment, f) adherence to their asthma controller medications and f) self-management support counseling. We will also calculate the relative cost-effectiveness, from the perspective of society and health plans, of providing patients with access to the interactive website.

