### 5. Procedures to be followed

Potentially interested participants will call a toll-free number and speak to a study coordinator, who will complete a phone screener. The phone screener includes questions in the following categories: basic demographic information, race and ethnicity, exclusion criteria questions, contact information (e.g., phone number) and social security information, so that we are able to mail compensation for participation in the study. Data from this phone screening process will be collected on paper and parts of this form will be later entered into the management module. During this phone screener, the study coordinator will explain the study, ask questions to determine eligibility and then ask once again if the patient may be interested in participating. If the participant is eligible and interested, the study coordinator will read the verbal consent document over the phone. If the participant is interested, eligible and consents to participate in the study over the phone, the study coordinator will inform the participant that he/she is included in the study and will receive an email within the next day from the study, explaining what will happen next. The coordinator will also inform the participant that upon logging into the application for the first time, they will have to read, review, and electronically agree to a Member Authorization Form by Highmark. They will be able to print out this form for their own records. Those that do not agree will not be allowed to participate. Those that do agree will then be randomized automatically, according to an algorithm written in the management module, to either the asthma or preventive care modules. The study coordinator will enter the specific screening information into the application (all screening fields except for mailing address and SSN) after their phone call with the participant and then check a box representing that the participant has completed the phone consent procedure. The participant will then be asked to use the website once every 30 day cycle and within 14 days of their next scheduled visit with their asthma care provider. At baseline, 6 months, and 12 months, they will be asked to complete specific measures online, as outlined below. During other monthly logins, they will be asked to complete short surveys that will then generate feedback based on their group they were randomized to. Women of child bearing potential will be asked monthly if they are currently pregnant and if they state that they are, they will be withdrawn from the study. At the close of the study, Penn State researchers will be authorized to provide Highmark with the names, DOB’s, gender and dates participants electronically agreed to the Member Authorization Form. Highmark will then provide Penn State researchers with access to claims data for all enrolled participants, for the 2 years prior to study participation and up to 2 years post enrollment. Asthma-related claims of hospitalization, outpatient visits, emergency department visits and medications will be examined.

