Controller to reliever ratio: There are generally two types of medicines for asthma; those used for quick relief of asthma symptoms (“relievers”), and those that are used daily to prevent asthma symptoms (“controllers”). Using a controller medication is the first step in managing persistent asthma, according to the treatment algorithm (page 343) on the 2007 NAEPP Guidelines 26, and has served as a main outcome measure in many quality improvement studies 66-68,104. By using more controller medicines, therefore, the number of reliever medicines tends to go down 105. The ratio of controller/reliever canisters is strongly predictive of future emergency department visits and, as such, has been used as a measure of asthma control and quality of care 105-107. As the intervention is designed to help individuals receive a controller medicine and, for those whose asthma is not controlled, often a second controller medicine, the controller to reliever ratio should be sensitive measure of the effects of the intervention. We will use standard ways to express this variable, which will be calculated as the ratio of the number of controller medications (i.e., inhaled corticosteroid) dispensed during the study year divided by the sum of the number of controller medications dispensed plus the number of canisters of inhaled relievers (e.g., short-acting beta-2-agonists) dispensed during the study year. This ratio ranges from 0 (no controller medications) to 1.0 (no reliever medications) 105-108. Grymonpre and colleagues observed that the concordance between claims data on medication acquisition and pill counts was between 79% and 88%, which were both highly significant 109. This data will be captured in the electronic claims data from Highmark, as none of the medicines are inexpensive, so patients should find it less expensive to use their prescription drug coverage through Highmark than to pay out of pocket. Similar methods are used by the National Committee for Quality Assurance to estimate the quality of asthma care in over 500 health plans nationally 7.

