Medication Adherence: The intervention, in some cases, will suggest that patients discuss medication adherence with their provider. This is based on the recommendation (page 336) that “before increasing therapy, however, the clinician should review the patient’s inhaler technique and adherence to therapy” 26. We will measure medication adherence to all asthma controller medications, such as inhaled corticosteroids and long-acting beta-2 agonists, using health care claims for asthma-related medications from Highmark. Health care claims have been shown to be a valid and reliable way to assess medication adherence 109. Our measure of adherence will be the Medication Possession Ratio (MPR), a commonly used measure of adherence, that is highly correlated with other measures of adherence and predictive of asthma exacerbations 111-116. The MPR measures the percentage of doses available to the patient during a specific time period. [name] has experience, through multiple clinical trials for asthma, in measuring adherence to asthma medications and will oversee analysis of medication adherence data 117,118 . Though medication adherence is not a main focus of the intervention, we hypothesize that, by encouraging patients to discuss medication adherence-related issues with their provider, patients in the IC will have higher rates of adherence to their controller medications than subjects in the CC.

**Moderating variables**: For our purposes, moderating variables are those that the intervention will not seek to modify, yet may lead to a differential response to the intervention.

Demographics: Age, gender, race, ethnicity, educational achievement, marital status and household income will be measured, using standardized instruments such as those from the Behavioral Risk Factor Surveillance System 119,120. These variables have been shown to be related to asthma prevalence, asthma quality of care and asthma-related quality of life 121-123. We will assess these variables at baseline and use the data to assess whether demographic variables, such as household income, moderate the effect of the intervention on inhaled corticosteroid use or asthma control.

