Secondary analyses: The secondary hypotheses, taken from the Specific Aims, are that subjects in the IC will have fewer asthma-related emergency department visits, greater gains in their asthma-related quality of life, greater increases in their controller-to-reliever medication ratio, greater satisfaction with asthma treatment and greater adherence to their asthma controller medications, after 12 months, than will patients in the CC. Statistical analyses for these hypotheses will follow the analytic plan as described for the primary outcomes. Secondary outcomes that are dichotomous (e.g. improved asthma-related quality of life) will be fit using the GEE approach with a logit link, which extends the logistic regression model, as described previously. Outcomes that are continuous (e.g. asthma control, adherence) will be analyzed using the linear mixed-effects model developed by Laird and Ware (1982) which extends linear regression to allow for repeated measurements. Ordinal measures will be estimated as a cumulative odds regression model 138 after satisfying the assumptions of proportionality between levels of the outcome and the explanatory variables. When this assumption cannot be satisfied, nonproportional models, such as logistic regressions between adjacent categories, will be examined.

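### The controller-ratio hypothesis predicts an increase, but the ratio is defined only in the study year, and no claims outcome has a pre-enrolment baseline

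*Protocol*

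**What the plan says.** **Hypotheses.** The Specific aims state that "at the end of 12 months, we hypothesize that IC subjects, compared to CC subjects, will have greater improvements in" a list that includes asthma-related emergency department visits, the controller/reliever ratio and adherence. Section 7, Secondary analyses, keeps change wording for the ratio, "greater increases in their controller-to-reliever medication ratio". It words the emergency outcome as a level, "fewer asthma-related emergency department visits", and does the same for adherence.

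**Measures.** Section 6 builds the ratio from controllers dispensed in the study year and the "number of canisters of inhaled relievers (e.g., short-acting beta-2-agonists) dispensed during the study year". For adherence it says "The MPR measures the percentage of doses available to the patient during a specific time period" and does not name the period. Emergency visits come from claims sent when the study ends, with no counting period given.

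**Data.** Section 5 gives the researchers claims "for the 2 years prior to study participation and up to 2 years post enrollment" and adds: "Asthma-related claims of hospitalization, outpatient visits, emergency department visits and medications will be examined". Its schedule of measures has one Claims column, not split into baseline and follow-up.

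**Covariates.** Section 7 adds baseline variables to the models when the arms turn out to differ on them. The secondary analyses follow the plan for the primary outcome.

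**The concern.** A hypothesis about an increase needs two values per subject, one before and one after. For the ratio the protocol defines only the later one. The aims also speak of improvement in emergency visits and adherence, and for these neither a reference period nor a follow-up period is fixed.

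Two things are at stake. First, the ratio hypothesis cannot be carried out as worded until someone chooses a baseline period, and that choice would otherwise be made when the claims are already in hand. Second, a subject's own value in the year before randomisation is likely to be among the best predictors of the same measure a year later. The protocol collects the claims needed to compute it and does not assign them that use.

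**Working it through.** **1. The plan's own figure.** The sample size rests on the Asthma Control Test, not on claims. Inputs from section 7: 70% versus 55%, two-sided alpha 0.05, power 80%, 20% loss. Equal allocation is assumed, since the ratio is not stated.

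n per arm = [1.960 × √(2 × 0.625 × 0.375) + 0.842 × √(0.70 × 0.30 + 0.55 × 0.45)]² / 0.15² = (1.342 + 0.569)² / 0.0225, about 162.3, so 163.

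Total 2 × 163 = 326, and 326 / 0.80 = 407.5, so 408. Both stated figures reproduce. No claims window enters the calculation, so nothing below alters it.

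**2. Hypothesis against definition.**

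| Claims outcome | Aims | Section 7 | Follow-up period in section 6 | Pre-enrolment value |
|---|---|---|---|---|
| Controller ratio | improvement | increase | study year | none defined |
| Emergency visits | improvement | level | not stated | none defined |
| Adherence (MPR) | improvement | level | not stated | none defined |

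The mismatch is sharpest for the ratio, where both statements of the hypothesis concern change and the definition supplies one value. Adherence has a related gap: section 7 names it for a mixed model for repeated measurements, but section 6 gives it one unspecified period and no occasions.

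**3. What an increase requires.** Write R = controllers / (controllers + relievers). With an assumed 8 controllers and 4 relievers in the study year, R = 8/12 = 0.667. The increase is R(study year) − R(pre-year). The second term has no definition in the protocol, although the same formula could be applied to the earlier dispensing claims.

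**4. What adjustment would give.** In a linear model,

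Y(post) = a + b·arm + c·Y(pre) + error.

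Subtracting Y(pre) from both sides gives

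Y(post) − Y(pre) = a + b·arm + (c − 1)·Y(pre) + error.

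The arm coefficient b is the same in both lines. An analysis of the study-year value adjusted for the pre-year value therefore also answers the between-arm question about change. If ρ is the within-arm correlation between the two years, the residual variance falls by a factor of about 1 − ρ². The protocol gives no ρ, so no figure is claimed.

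**5. Whether the plan already does this.** Covariates enter when the arms differ at baseline, so a pre-year value would be used only after a chance imbalance, and only if someone had computed it. The dropout comparison mentions baseline controller use, but does not define it or make it the baseline for a claims outcome.

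**6. Whether the data exist.** The pull reaches 2 years back, and eligibility requires an asthma encounter and at least 3 months of asthma medication in the past year. A pre-year value should be obtainable for anyone covered by the plan throughout that year.

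**The case against.** The best defence is that section 5 describes access to data, not an analysis window. The hypotheses are set at 12 months, outpatient claims are reviewed at the end of the 12-month study, and exact windows are often left to an analysis plan, which is not shown here. This largely stands for the emergency-visit and MPR windows. It does not settle the ratio, where two parts of the protocol disagree about what is measured.

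It can also be said that, under randomisation, the arms have equal expected pre-year values, so a comparison of study-year levels estimates the same between-arm difference as a comparison of changes. That is correct, and it means the level comparison is not biased. It still cannot show that the ratio rose, and it forgoes the precision of the pre-year value.

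Three stronger readings are tempting and are not supported:

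- A reader might infer that 2 years before against up to 2 years after makes the periods incomparable. The protocol nowhere proposes comparing whole-pull counts. A matched pair of 12-month periods lies within the pull, provided claims are drawn after each subject's study year. Unequal lengths would affect both arms alike in expectation if claims follow-up is balanced. Under constant dispensing the ratio does not depend on length: 8/12 = 16/24 = 0.667.
- A reader might infer that second-year time dilutes the effect. Assume uniform accrual over 0.5, 1 or 1.5 years, a claims cut at the last subject's month 12, and a first-year rate ratio of 0.70 that vanishes afterwards. Mean follow-up is then 1.25, 1.50 or 1.67 years. The pooled ratio, (0.70 + mean − 1)/mean, is 0.76, 0.80 or 0.82. These figures apply only if all post-enrolment claims are pooled, which the protocol does not say.
- Section 6 lists health care utilization under primary outcome measures, so a reader might think the primary analysis is affected. Section 7 names the dichotomised Asthma Control Test at 12 months as the primary outcome.

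**Conclusion.** The point holds in a limited form. The ratio hypothesis concerns a change that the ratio's definition cannot yield. None of the three claims outcomes in the hypotheses has a pre-enrolment value defined or used in the arm comparison, although the claims to compute one are obtained. The severity is minor: the primary outcome and the 408 subjects are unaffected, and no bias in the randomised comparison is shown.

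The benefit of acting is a testable ratio hypothesis and some added precision. The precision claim assumes that the pre-year and study-year values are correlated and that most subjects were covered for the full prior year; the protocol quantifies neither.

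**What to change.** In section 6 (emergency department visits, controller to reliever ratio, medication adherence) and section 7 (Secondary analyses):

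- Measure emergency visits, the controller ratio and the MPR over days 1 to 365 after randomisation.
- Compute the same measure over days -365 to -1 as its baseline.
- Compare arms on the study-year value, adjusted for the pre-year value in every case and not only after an observed imbalance. Word all three hypotheses to match.
- State that claims after day 365 are descriptive, for example of persistence, so that time after the intervention stays out of the 12-month comparison.

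This takes protocol wording and programming on claims that are already authorised. The one real cost is that second-year claims would not count toward the 12-month hypotheses.

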### 6. Primary and secondary outcome measures

**Primary Outcome measures:** Asthma control, health care utilization, pulmonary function and asthma-relate quality of life. The main aim of the intervention is to improve asthma control and improve quality of care for asthma, in keeping with the 2007 NAEPP Guidelines 29. The NAEPP guidelines state that the goals include “minimal or no chronic symptoms day or night” and “no limitations on activities” 29. We hypothesize that each of these measures will be improved in the IC, compared to the CC.

Asthma Control: We will measure asthma control using the Asthma Control Test (ACT), at baseline, 6 months, and 12 months. The ACT asks patients about several aspects of their asthma control over the past 4 weeks: a) whether their asthma interfered with their activities, b) how often they had shortness of breath from asthma, c) how often they used their rescue inhaler, d) how often they had asthma symptoms at night and e) an overall impression of their asthma control. The ACT has a test-retest reliability of 0.84 and compares closely with a specialist’s rating of asthma control, the need for change in patient’s therapy and percent predicted FEV1, future asthma control and future emergency department visits 98-100. The ACT is also sensitive to changes in asthma treatment 99. The overall agreement between ACT and the specialist’s rating ranged from 71% to 78% depending on the cut points used, and the area under the receiver operating characteristic curve was 0.77 98. An ACT score of ≥ 20 will be used as a cutoff for determining “controlled” v. “uncontrolled” asthma, as this cutoff demonstrated the highest area under the ROC curve. The use of the ACT, as well as the cutoff of 20 for determining control are supported in the 2007 NAEPP Guidelines on page 345 26. We hypothesize that, at 12 months, 70% of subjects in the IC condition will have an ACT of ≥ 20 versus only 55% in the CC condition.

Asthma-Related Emergency Department Visits: Improvements in asthma control can decrease future use asthma-related emergency room visits, so we will measure asthma-related emergency department visits 6,100,101. Claims data are valid measures, and superior to other means, such as self-report, for measuring asthma-related emergency department visits. 102,103. Highmark will send us claims data, at the end of the study, which will identify asthma-related emergency department claims. This is data that is already being analyzed by Highmark, in ways that are standardized by the National Committee for Quality Assurance (NCQA), for reporting the quality of care delivered to patients with asthma 7. In the NCQA reporting, asthma-related emergency department visits are one way to identify patients with persistent asthma 7. We will take advantage of that reporting mechanism in the current study.

Asthma Control and Quality of Life: We will use questions about asthma control and quality of life from the National Asthma Survey, from the CDC and published by Halterman and colleagues (Halterman, Aligne et al. 2000). The instrument identifies several aspects of asthma control and how it impacts quality of life, including days with symptoms, days symptom-free, emergency room visits, urgent doctor visits, asthma attacks, severity of asthma attacks and the degree to which asthma impairs function. It is not clear how many of these questions are validated, but they are used as outcome studies in a great number of asthma clinical trials and have strong face validity and national norms is helpful. Drs. [name], [name] and [name] are working on the adult version of the Halterman paper, using the data from the NAS.

**Mediating Variables:** For our purposes, mediating variables are those that the intervention will attempt to modify in order to bring about a change in asthma control and quality of care for asthma. We will examine variables that have been associated with asthma control and quality of care for asthma and those that have been targeted by the intervention and therefore may mediate the effect of the intervention on the above outcome variables. We hypothesize that each of these variables will mediate the effect of the intervention.

Intervention fidelity: Use of interactive website before asthma care provider visits. Use of the interactive website will be tracked passively. Each login by study subjects will be recorded, as will the duration of each login, the number of pages viewed, any data entered and the number of times that subjects received the computer-tailored feedback. The active part of the intervention is felt to be the computer-tailored feedback, so this measure will represent the “dose” of the intervention. Dose will be measured as a proportion of asthma provider visits before which the website was used, expressed as a percentage. The number of visits with an asthma care provider will be obtained from chart review, and will be the denominator for this measure. The number of visits that subjects used the website within two weeks prior to these visits will be the numerator for this measure. We consider visits to an asthma care provider to be any visits to the patients’ primary care provider as well as any visits that the patient had with a pulmonary medicine specialist during the study. Upcoming visit dates will be tracked using brief monthly emailed surveys to patients. These surveys will seek to clarify the date(s) of planned visits to asthma care providers, including primary care providers and specialists. All patients who have not used the website within 14 days before their planned visit to an asthma care provider will be sent an automated email reminder, encouraging subjects to use the site or to use a toll-free number to call the study staff if they are having trouble using the website. These email reminders will be repeated 7 days before their next doctor visit and then 3 days before if they have still not used the website. These methods were successful at ensuring a 90% fidelity rate in a pilot RCT of the website 25,27.

Controller to reliever ratio: There are generally two types of medicines for asthma; those used for quick relief of asthma symptoms (“relievers”), and those that are used daily to prevent asthma symptoms (“controllers”). Using a controller medication is the first step in managing persistent asthma, according to the treatment algorithm (page 343) on the 2007 NAEPP Guidelines 26, and has served as a main outcome measure in many quality improvement studies 66-68,104. By using more controller medicines, therefore, the number of reliever medicines tends to go down 105. The ratio of controller/reliever canisters is strongly predictive of future emergency department visits and, as such, has been used as a measure of asthma control and quality of care 105-107. As the intervention is designed to help individuals receive a controller medicine and, for those whose asthma is not controlled, often a second controller medicine, the controller to reliever ratio should be sensitive measure of the effects of the intervention. We will use standard ways to express this variable, which will be calculated as the ratio of the number of controller medications (i.e., inhaled corticosteroid) dispensed during the study year divided by the sum of the number of controller medications dispensed plus the number of canisters of inhaled relievers (e.g., short-acting beta-2-agonists) dispensed during the study year. This ratio ranges from 0 (no controller medications) to 1.0 (no reliever medications) 105-108. Grymonpre and colleagues observed that the concordance between claims data on medication acquisition and pill counts was between 79% and 88%, which were both highly significant 109. This data will be captured in the electronic claims data from Highmark, as none of the medicines are inexpensive, so patients should find it less expensive to use their prescription drug coverage through Highmark than to pay out of pocket. Similar methods are used by the National Committee for Quality Assurance to estimate the quality of asthma care in over 500 health plans nationally 7.

Outpatient asthma care provider visits: The intervention will suggest to some patients, based on rules in the 2007 NAEPP Guidelines, to see an asthma care provider sooner than scheduled (page 345) or to see an asthma specialist (page 288) when none had been seen. It is therefore important to capture these measures of treatment effects. To understand the frequency and timing of primary care and specialist visits for asthma, we will review the Highmark claims database at the end of the 12 month study. The names of providers who are seen will be compared to a database of generalist and specialist physicians that we have used in the past, from SK&A, Inc. Asthma care providers will be determined to be of two types: a) any pulmonologist or allergist seen by the patient, b) any primary care provider seen by the patient who prescribed at least one asthma-related medication during the 12-month study. Visits to these providers will be determined by identifying Highmark claims.

Asthma Self-Management Support Counseling: The 2007 NAEPP Guidelines, as well as previous versions, recommend that physicians should counsel their patients about several aspects of self-management, including recognizing early symptoms of asthma, changing their environment to improve asthma control and creating an asthma action plan 26,29,110. To measure the delivery of this care, we will use standardized measures from the 2003 National Asthma Study, summarized in the National Healthcare Quality Report 9,10. Using this protocol, we will ask specific questions about counseling they received, over the past year, about recognizing early symptoms of asthma, changing their environment to improve asthma control and creating an asthma action plan.

Medication Adherence: The intervention, in some cases, will suggest that patients discuss medication adherence with their provider. This is based on the recommendation (page 336) that “before increasing therapy, however, the clinician should review the patient’s inhaler technique and adherence to therapy” 26. We will measure medication adherence to all asthma controller medications, such as inhaled corticosteroids and long-acting beta-2 agonists, using health care claims for asthma-related medications from Highmark. Health care claims have been shown to be a valid and reliable way to assess medication adherence 109. Our measure of adherence will be the Medication Possession Ratio (MPR), a commonly used measure of adherence, that is highly correlated with other measures of adherence and predictive of asthma exacerbations 111-116. The MPR measures the percentage of doses available to the patient during a specific time period. [name] has experience, through multiple clinical trials for asthma, in measuring adherence to asthma medications and will oversee analysis of medication adherence data 117,118 . Though medication adherence is not a main focus of the intervention, we hypothesize that, by encouraging patients to discuss medication adherence-related issues with their provider, patients in the IC will have higher rates of adherence to their controller medications than subjects in the CC.

**Moderating variables**: For our purposes, moderating variables are those that the intervention will not seek to modify, yet may lead to a differential response to the intervention.

Demographics: Age, gender, race, ethnicity, educational achievement, marital status and household income will be measured, using standardized instruments such as those from the Behavioral Risk Factor Surveillance System 119,120. These variables have been shown to be related to asthma prevalence, asthma quality of care and asthma-related quality of life 121-123. We will assess these variables at baseline and use the data to assess whether demographic variables, such as household income, moderate the effect of the intervention on inhaled corticosteroid use or asthma control.

Health Literacy: Several studies have identified the link between health literacy and a wide variety of health outcomes 124-127. As the intervention to be tested includes written health-oriented messages, the effects of these messages may be dependent on the individuals’ level of health literacy. To measure health literacy, we will use the Short Form Test of Functional Health Literacy in Adults (s-TOFHLA), which is valid and reliable and is shown to be associated with control of chronic illnesses 124-127. The abbreviated form of the s-TOFHLA is a 36-item timed reading comprehension test with multiple choice responses, and contains two health passages. The test is scored on a scale from 0 to 36. Though we will make sure that all feedback is written at not more than the 6th grade reading level, we hypothesize that the effect of the intervention will be greater among patients with higher levels of health literacy.

Health-related Internet use: We will measure subjects’ use of the Internet for health-related activities, using a survey instrument from the Pew Internet and American Life Project 86,87,128,129. The instrument measures the use of the Internet for a variety of health-related activities (e.g., looking for information about medications). These survey questions will be asked at baseline and at 12 months. As each recommendation in the computer-tailored feedback includes a link to another reputable website with information on the topic, we hypothesize that the effect of the intervention will be greater among patients who have the greatest increases in using the Internet for health-related information.

